### Study population and recruitment procedure

The process of the three online-RCTs, each with parallel groups and equal distribution, is presented in the flowchart (Fig. 1).

**Fig. 1 Fig1:**
[figure not shown]
Flowchart of three RCTs to evaluate the *TK-HealthCoach*. See Table 4 for sample size details. *N* = absolute number; *t* = measurement time point

### Inclusion criteria

Healthy persons (male/female/diverse*)*, aged 18 years and older, regardless of whether they are insured with *TK health insurance fund*, are eligible to participate. Interested persons with impairments or pre-existing conditions require a medical assessment as to whether the program is suitable for them. Participation is only permitted on the condition that interested persons provide truthful information with regard to their health status. Each person can only choose one health goal and therefore participate in only one RCT.

### Specific inclusion criteria for the “Smoking Cessation” RCT

Only people who smoke at baseline (t0) can take part in the “Smoking Cessation” online RCT.

### Specific inclusion criteria for semi-standardized telephone interviews

Only participants in the “Smoking Cessation” online RCT’s intervention group and those who have completed the t1 online questionnaire can register for these interviews.

### Exclusion criteria

People will be excluded from participating in the program or study if
Their health impairments which, according to a medical assessment, partially or completely rule out participation in the chosen online health program,They are already participating in another study aiming to change behavior towards the health goal in question.

### Specific exclusion criteria for the Losing and Maintaining Weight RCT

Pregnancy or breastfeeding,Waist circumference > 200 cm or body mass index (BMI) > 40 kg/m^2^,Currently underweight or underweight after a weight loss of 3 kg,

Interested persons are asked to calculate their BMI (link offered).

### Specific exclusion criteria for the Increasing Fitness RCT

Pregnancy,Currently underweight

Persons with waist circumference > 200 cm or BMI > 40 kg/m^2^ must obtain a medical assessment that allows participation in the health program.

Interested persons are asked to calculate their BMI (link offered).

### Specific exclusion criteria for the Smoking Cessation RCT

Interested persons cannot participate if they have already quit smoking, even if it is only for a few days.

### Specific exclusion criteria for the telephone interview

Any restrictions making a telephone survey impossible, such as severe communication difficulties.

### Recruitment procedure

From January 1 to 17 of June 2020, a total of *N* = 2903 study participants have to be recruited in all RCTs, including the local medical substudies. The number of participants who have to be enrolled in the online studies is N = 2567.

Recruitment activities and information are being disseminated via online and print media. These include various information provided via channels of the *TK health insurance* (websites, newsletters, blogs etc.), advertisements on Google, and different health media. Advertisements in the local press and radio, the intranet of the University of Freiburg and its Medical Center, and a local display of flyers serve to recruit specifically for the regional medical substudies.

People intending to change their health behavior find brief information about the study and its objectives on the project’s homepage. As specific inclusion and exclusion criteria apply to each of the three programs or RCTs respectively, detailed study information is provided on each program entry.

If interested persons give their informed consent to participate in the program and study, and after completing their registration, they will as participants receive the first health goal-specific questionnaire by e-mail (baseline t0).

Participants in the *Increasing Fitness* or *Losing and Maintaining Weight* RCTs living in the postal code area 79 are offered the possibility to enroll in the medical substudies after filling out the t0 questionnaire. These substudies entail sports and nutritional medical examinations (details will be published in the study protocol of the medical substudies).

### Randomization

After completing the baseline questionnaire, the online RCT participants are given access to their selected online health program. While accessing the program, the participants in each online RCT are allocated at random to the interactive online health program (intervention group) or the non-interactive online health program (control group). Randomizations take place separately for each RCT *Increasing Fitness*, *Losing and Maintaining Weight*, and *Smoking Cessation* via permuting block randomization with variable block sizes of 4, 6, and 8. The participants are assigned to the intervention or control group automatically according to randomization lists. These randomization lists for each RCT were created by SEVERA, applying the software RITA, version 1.50 [19], and transmitted on May 28, 2019, to the IT Company (Vilua Healthcare GmbH), responsible for operating the online program and online survey. The randomization lists cannot be influenced by participants, the IT Company, or the health program’s provider.

We chose permuting block randomization to ensure equal distribution in the intervention and control groups in case of deviations between the numbers of targeted and indeed enrolled participants.

Blinding of the study participants is not possible due to their informed consent to participate in one of two different health-program forms (interactive vs. non-interactive). By participating actively in the interventions, they will be immediately aware of the group to which they have been allocated. Blinded data analysis cannot be ensured either, since the data collected may indicate the study-arm affiliation.

## Interventions

All study participants are given access to a health goal-specific, web-based online program with the difference being that the intervention group is offered a comprehensive, interactive program and the control group a less extensive, non-interactive program.

All participants have access to a personal profile page where they find their personal registration data, study information, and declaration of consent as well as the possibility to unsubscribe from the study and/or program.

### Intervention groups

Participants in the intervention groups are given access to the technically guided, interactive programs *FitnessCoaching*, *WeightLossCoaching*, or *SmokingCessationCoaching*.

The recommended duration of participation in *FitnessCoaching* and *WeightLossCoaching* is 12 weeks, that in *SmokingCessationCoaching* 6 weeks.

The overall aim of each coaching module is to guide users step by step to their health goal and prepare them to continue after the coaching. For this, the users are asked to compile their activities and will then receive a tailored plan and technically guided psychological input to achieve sustainable, positive health effects. Each coaching module contains specific tools to help avoid relapsing. In addition, participants are advised by experts from the IT Company on request.

*Individual action planning*: A common feature of the three coaching modules is their multimodality, interactivity and individual applicability. Each program starts with an anamnesis specific to the chosen health goal. Based on those results, participants plan individual activities with adaptable intensity. All selectable activities are accompanied by video-, audio- or reading instructions. Since many activities benefit different health goals, the participants can choose their individual activities across all three coaching modules—with the exception that the *SmokingCessationCoaching* activities cannot be selected by participants in *FitnessCoaching* or *WeightLossCoaching*.

To enhance health-related knowledge, users are given access to a comprehensive, evidence-based knowledge area divided into different articles. The program pre-filters relevant content for the user. Nevertheless, each user in the intervention group can access all information, regardless of their coaching module.

Weekly planned activities, specific articles, and advice as well as test-tools and daily motivation tips are displayed on an individual dashboard personalized to accommodate each user’s current progress.

*Logging results, feedback, and motivation*: All activities carried out, data from activity trackers, self-tests, nutrition and smoking protocols, as well as read articles, etc., can be logged on by participants. Pop-up toasts or notifications depending on the progress of the participants give feedback on attained goals, motivate user to continue, or suggest specific barrier management. The latter is implemented in the *FitnessCoaching* and the *SmokingCessationCoaching*.

A personal profile page contains an overview of each participant’s progress in weight loss and physical activity or days not smoking. It also contains the study information and informed consent form as well as buttons to withdraw participation in the study or program. At the end of each coaching module (after 6 or 12 weeks, respectively), a review page containing an overview of each participant’s goals and attainments is displayed.

#### Specificities of the coaching modules

The *WeightLossCoaching* focuses on a sustainable change in diet and the principle of balanced nutrition. The aim is that participants reduce their weight by a maximum of 5 kg within a 12-week period. Its main tool, based on the concept of energy density [20], is a comprehensive protocol of nutrition and physical activity by which an individual’s optimal energy requirements are calculated. An extensive cookbook with recipes is available.The *FitnessCoaching* main elements are training plans for strength, endurance, and mobility characterized by progressive training loads through various sports activities such as pilates, back training, yoga, circuit training, Nordic walking, jogging, and cycling. Additional physical activities can be added.The *SmokingCessationCoaching* applies the cold-turkey strategy and has a modular structure. Users can get themselves ready for the smoking-cessation date during a preparation phase lasting a maximum 14 days, followed by a 4-week weaning phase. The *SmokingCessationCoaching* includes meditation and mindfulness modules. Additionally, participants are invited to take part in an individual telephone counseling entailing up to four consultations. The counselors are especially trained to carry out this intervention (for details see supplement 1) (Table 1).

**Table 1 Tab1:** Number of specific components of each coaching module

	Interactive self-tests/courses	Specific activities	Specific articles/videos	Individual tips	Cooking receipts/receipt videos	Physical exercises/videos
			Number *N*			
WeightLossCoaching	3 /1	13	18/18	503	2500/300	
FitnessCoaching	5/1	13	29/20	126		170 /147
SmokingCessationCoaching	4/2		29 /12	32		

The participants can choose their individual activities across all three coaching modules—with the exception that the SmokingCessationCoaching activities cannot be selected by participants in FitnessCoaching or WeightLossCoaching

### Control groups

The control group participants are given access to a non-interactive online health program according to their selected health goal. They receive evidence-based information with advice to attain their goals. This information is divided into different lessons on a website especially designed for each health goal. Study participants are unable to link training plans, protocols or data from activity trackers to the program. A personal profile page contains study information, the informed consent form, and buttons to withdraw participation in the study or program.

After the trial-dependent program ends, all participants, regardless of their study arm, will be given access to the trial-independent interactive *TK-HealthCoach*. This will be possible for all persons regardless of their membership in the *TK health insurance fund*. While the development of each trial-dependent coaching module (used by study participants) was concluded at the beginning of the study, the trial-independent *TK-HealthCoach* has been expanded to incorporate new coaching modules, i.e., *AntistressCoaching*.

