## Methods/design

### Study aim, design, and setting

The aim of this study is to test the long-term effectiveness of the *TK-HealthCoach* with regard to these primary outcomes: increased physical activity, weight loss, and smoking abstinence. An online randomized controlled trial (RCT) of parallel design is being conducted as part of the summative evaluation for each of the three health goals *Increasing Fitness*, *Losing and Maintaining Weight*, and *Smoking Cessation*. The aim is to examine if participants of interactive online programs achieve higher effects on study outcomes than participants of non-interactive programs.

Adults across Germany intending to lose weight, increase their fitness or quit smoking are invited to participate in one of the online studies. We are planning to recruit a total of approximately *N* = 2567 participants in the three online RCTs. In addition to these online RCTs, the Department for Sport and Sport Science (IfSS), University of Freiburg is conducting two medical substudies on the health goals *Increasing Fitness* and *Losing and Maintaining Weight*. The aim of these two substudies is to determine long-term physiological effectiveness as a result of behavioral changes. Since the precondition for participating in either substudy is to fill out the online questionnaires, the total number of participants to be recruited has to increase by *n* = 336 to *n* = 2903 (sample size calculation see Table 5).

Formative evaluations will be conducted in addition to the *TK-HealthCoach’*s summative evaluation. These include (a) detailed quantitative analyses of usage behavior data and (b) qualitative interviews with persons participating in the intervention group of the online RCT *Smoking Cessation*.

Study period of each RCT includes the program runtime of the health goals (*Smoking Cessation*: six weeks; *Increasing Fitness* and *Losing and Maintaining Weight*: 12 weeks) as well as another twelve-month follow-up after the program’s completion.

Participant data is being captured via online questionnaires at these time points:
Baseline t0: after registration and before the program startsFollow-up t1: after completing the program
*Smoking Cessation*: after 6 weeks*Increasing Fitness* and *Losing and Maintaining Weight*: after 12 weeksFollow-up t2:

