*Smoking Cessation*: 4 months after completing the program*Increasing Fitness* and *Losing and Maintaining Weight*: 6 months after completing the programFollow-up t3: 12 months after completing the program in all three RCTs.

The data on program usage will be recorded during the entire study period.

In the RCT *Smoking Cessation* qualitative telephone interviews will be carried out once the t1 questionnaires have been completed.

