### Research questions and hypothesis

The following questions and hypotheses are being investigated in this study
What effects do the online programs within the three health goals *Losing and Maintaining Weight*, *Increasing Fitness*, and *Smoking Cessation* have on the primary and secondary outcomes variables reported by participants?We assume that we will observe statistically significant improvements with small to medium effect sizes for each program.Will the intervention groups (interactive health programs) in each RCT reveal stronger effects on primary and secondary outcomes in comparison to the control groups (non-interactive health programs)? We will test the hypothesis that the intervention groups’ changes in the primary and secondary outcomes are more positive than the control groups’. Our focus is on long-term effects so we will analyze the change between baseline (t0) and 1 year after the intervention finishes (t3), while short-term effects are part of the secondary analyses. We expect small to medium effect sizes from the comparison between these two groups.Does the intensity of use of health programs have an impact on their effects?The hypothesis we test is that study participants who use their health program more frequently and intensively achieve better outcomes than study participants who use the program less often or less intensively.How satisfied with the programs offered are the study participants in the intervention- and control groups? This question will be examined exploratively in secondary analyses.

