**Basic variables**							
Membership in health insurance	Self-developed/percentages	W, F, S	1	**x**			
Knowledge of the study	Self-developed/percentages	W, F, S	1	**x**			
Experience with online health programs	Self-developed/means and percentages	W, F, S	1	**x**			
Current use of (other) online health programs	Self-developed/percentages	W,F,S	6	**x**	**x** (6)	**x**(6)	**x** (6)
Further internet use in general and regarding health subjects	Self-developed/percentages	W, F, S	10	**x**	**x** (1)	**x** (1)	**x**(1)
Previous attempt at behavior change	“Berlin Risk Appraisal and Health Motivation Study” (BRAHMS [50]); adapted to specific health goal/means	W, F, S	2 4	**x**			
Actual health behavior	Self-developed/percentages	W, F, S	1	**x**	**x**	**x**	**x**
Height	IRES [48] (Use for calculation of Body mass index)	W, F, S	1	**x**			
Smoking	Self-developed/percentages	W, F	1	**x**			

Health goals: W=”Losing and Maintaining Weight”; F=”Increasing Fitness”, S=” Smoking Cessation”;

measurement time point: t0 = Baseline, t1 = first follow-up; t2 = second follow-up; t3 = third follow-up; IRES = Indicators of rehabilitation status

**Table 3 Tab3:** Variables of three health goal-specific questionnaires: primary outcomes and secondary outcomes

Variables/Constructs	Source/Origin/Analyses	Health goal	Number of items	Time measure points			
				t0	t1	t2	t3

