#### Incentives

After the trial-dependent program ends, all participants, irrespective of their study arm, will be given access to the trial-independent, interactive *TK-HealthCoach*. This is possible for all study participants regardless of membership in the *TK health insurance fund*. While the development of the trial-dependent programs (those used for study participants) was stopped at the beginning of the study, the trial-independent *TK-HealthCoach* is being expanded with new Coaching modules such as *AntistressCoaching*.

Participants who filled out all four questionnaires will receive a shopping voucher worth € 25. For returning the t1 and t2 questionnaires participants will receive discount coupons for the purchase of activity trackers. Interview partners will receive in addition a shopping voucher worth € 30. All vouchers will be sent by e-mail.

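### Both arms get the interactive coach once the 6- or 12-week programme ends, so the main contrast at t3, a year later, compares immediate with delayed access

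*Protocol article*

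**What the plan says.** - **Access (Control groups).** "After the trial-dependent program ends, all participants, regardless of their study arm, will be given access to the trial-independent interactive" TK-HealthCoach. The Incentives section repeats it: "irrespective of their study arm, will be given access to the trial-independent, interactive" coach. Neither section gives a calendar date or mentions waiting for t3.
- **Programme end (Intervention groups; Study aim, design, and setting).** A review page appears "At the end of each coaching module (after 6 or 12 weeks, respectively"). The study period is the programme runtime "as well as another twelve-month follow-up after the program’s completion".
- **Endpoint timing.** t1 follows programme completion, and t3 is "12 months after completing the program in all three RCTs".
- **Main contrast (Research questions and hypothesis).** "Our focus is on long-term effects so we will analyze the change between baseline (t0) and 1 year after the intervention finishes (t3"). Short-term effects are secondary. The stated aim is to learn whether interactive programmes do better than non-interactive ones.
- **Analysis (Summative evaluation).** The main analysis is by intention to treat in all randomised participants, with a group-by-time term over the measurement points. Adjustment is for health status, social support and similar factors, sex, age and the baseline outcome. Use of the coach after the programme has no role in the treatment contrast.
- **Related data (Table 2).** "Current use of (other) online health programs" is asked at all four time points and summarised as percentages.
- **Sample size (Table 5).** It allows for 50% dropout and a buffer of about 10%, but not for crossover.

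**The concern.** Randomisation controls who has the interactive coach only while the trial programme runs. After that, controls may use an interactive coach from the same provider for the whole year before the endpoint. Any benefit they gain from it is counted in the control arm at t2 and t3, which would most plausibly draw the arms together.

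What is at stake is the reading of a null result. If the arms do not differ at t3, the data cannot separate two explanations: the interactive programme has no lasting advantage, or controls caught up by using the interactive product. The protocol asks the first question, and the t3 comparison as laid out does not isolate it.

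**Working it through.** **1. Timing.** Taking 12 months as 52 weeks:
- Smoking: access differs by arm for 6 of 6 + 52 = 58 weeks, so 52/58 = 90% of the time to t3 falls after access opens to both arms.
- Fitness and weight: access differs for 12 of 12 + 52 = 64 weeks, so 52/64 = 81% falls after.

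**2. Reproducing the plan's sample sizes** (Table 5; two-sided alpha 0.05, power 0.80):
- Fitness, d = 0.25, two-sample t test: 252.13, rounded up to 253 per arm. Weight uses the same 253, because footnote 3 sizes it on physical activity as key secondary outcome.
- Smoking, 15% versus 2%: 77 per arm gives 80.1% power with Fisher's exact test.
- Dropout: 253/0.5 = 506 and 77/0.5 = 154 per arm. Buffer: 1012 × 1.1 = 1113.2, so 1114; 308 × 1.1 = 338.8, so 339.

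The stated figures reproduce, and crossover enters none of them.

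**3. Effect of control uptake.** The documents give access, not uptake, so a share c is assumed. Suppose a share c of controls gains the full intervention effect by t3 and continued access adds nothing in the intervention arm. Then:
- for a mean difference, d becomes d × (1 − c);
- for smoking, control abstinence becomes 2% + 13% × c.

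| c | Fitness d | Power, 253 per arm | Weight d | Power, 253 per arm |
|---|---|---|---|---|
| 0 | 0.250 | 80% | 0.50 | over 99% |
| 0.20 | 0.200 | 61% | 0.40 | 99% |
| 0.30 | 0.175 | 50% | 0.35 | 98% |
| 0.40 | 0.150 | 39% | 0.30 | 92% |

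If the buffer is fully recruited and dropout is exactly 50%, 1114 × 0.5 / 2 = 278.5, or about 278 per arm. Fitness power is then 84% without uptake and 65% at c = 0.20.

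Smoking, 77 per arm, Fisher's exact test, intervention rate 15%:

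| Control rate at t3 | Implied c | Power |
|---|---|---|
| 2% | 0 | 80% |
| 4% | (4 − 2)/13 = 15% | 57% |
| 6% | (6 − 2)/13 = 31% | 36% |

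**4. Whether access can still be delayed.** Recruitment closed on 5 October 2020 (Trial status). Twelve weeks later is about 28 December 2020; adding the eight-week response limit (Data management) gives about 22 February 2021. The article appeared on 10 August 2021. If the last participants started the programme promptly, everyone was past t1 by then. The last t3 assessments, 12 months after programme end, fall around the end of December 2021.

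**The case against.** - **Timing is inferred.** The text says access opens after the programme ends and gives no date; the 6 or 12 weeks are called a recommended duration. This stands as a caution. Still, opening at programme end is the natural reading, and no section says otherwise.
- **Size is hypothetical.** No uptake figure exists, and late users may gain less than the full effect. This stands: the power figures show sensitivity and do not predict a loss.
- **Not all three trials suffer equally.** A reader might infer that every primary comparison is seriously weakened. The plan's own figures do not support that: the weight primary outcome, at d = 0.50, is barely affected. Physical activity in that trial, the key secondary outcome that set its sample size at d = 0.25, has the same exposure as the fitness trial.
- **The endpoint is not purely t3.** The model uses repeated time points, and for smoking the Summative evaluation names the post-intervention difference as the effect size, which precedes most of the possible crossover. This stands, but it sits uneasily with the t3 focus in the hypotheses.
- **It is partly covered.** The Table 2 item is asked at t1 to t3, and the sensitivity section will consider programme use between arms. Neither expressly covers later use of the trial-independent coach. A detailed crossover analysis may be left to an analysis plan that is not shown; which question the t3 contrast answers is fixed by the protocol itself.
- **Access was a deliberate incentive.** An intention-to-treat comparison of immediate with delayed access remains a valid randomised comparison. That is correct, and it is why the remedy is to name the comparison accurately.

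**Conclusion.** The concern holds as a point about interpretation. As written, the t3 contrast estimates the effect of immediate versus delayed access to an interactive coach, while the stated question is interactive versus non-interactive. The likeliest bias is toward no difference, because both arms receive access. A positive t3 result would therefore stand; a null one would be ambiguous.

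The size rests on assumed uptake with full late benefit. On that basis fitness power falls from 80% to 61% at 20% uptake and 50% at 30% (84% to 65% at 20% with the buffer). Smoking power falls from 80% to 57% or 36% at about 15% or 31% uptake. The weight primary outcome stays at about 98% at 30%.

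A reader might go further and call the t3 comparison invalid, or conclude that the trials are underpowered. The documents support neither: randomisation and intention to treat are intact, and uptake is unknown. This should be fixed, but it does not undermine the trials.

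**What to change.** 1. State that the t3 contrast estimates immediate versus delayed access to the interactive coach.
2. Report use of the interactive coach after t1 by arm, from the Table 2 item on other online programmes at t1 to t3 or from platform logs. First confirm that these sources identify the TK-HealthCoach.
3. Prespecify one sensitivity analysis that treats control uptake as an intercurrent event.
4. Rest the uncontaminated interactive versus non-interactive claim on t1, and reconcile the smoking effect size at post-intervention with the t3 focus in the hypotheses.
5. If access was meant to open only after t3, say so in the Control groups and Incentives sections.

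Delaying access is probably no longer possible for this cohort, since recruitment has closed; items 1 to 4 can still be settled before the last t3 data arrive. The cost is wording, one extra analysis and a narrower t3 claim.
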